### Randomization and allocation concealment

The included participants will be randomly allocated to either the active acupuncture group (intervention group) or sham acupuncture group (placebo-control group) after the baseline assessment. We will use a computer program (Random Allocation Software, version 1.0; Msaghaei) [15] to generate random numbers. Block randomization will be used to ensure a balance in the number between the two groups. The list of randomization numbers will be kept by research staff who will be responsible for assigning the recruited patients to the corresponding intervention code based on the list. He or she will not be involved in patient care, outcome assessment, data collection or data analysis. The study flowchart is shown in Fig. 1.

**Fig. 1 Fig1:**
[figure not shown]
Study flow chart

### Blinding

All the participants, outcome assessors and clinical investigators will be kept blind to treatment allocation during the whole study. Owing to the nature of acupuncture, it is not feasible to blind the acupuncturists who perform the treatment procedure. However, they will be instructed to keep interaction with the patients to a minimum during the treatment period. Except for emergency cases, the blinding code will not be opened during the study period. To test the success of masking, a direct question will be asked to the participants: “Before the study was conducted, you were informed that you have equal chance to receive real acupuncture treatment and placebo-sham acupuncture treatment. After that, which treatment do you think you have received?”

### Interventions

Participants randomized to the intervention group will receive a standardized 30-min acupuncture treatment session in addition to standard routine care. The definition of standard routine care of overactive bladder in the Hong Kong hospital setting is all the conventional treatments except for medication, such as behavioral and physical therapy. From the Chinese medicine perspective, the pathogenesis of overactive bladder symptoms is mainly attributed to insecurity of kidney qi [16]. Pursuant to the traditional acupuncture theory, previous relevant studies and the opinion of acupuncture experts of the research team at the School of Chinese Medicine, CUHK, the following acupuncture points will be selected: BL32 (Ciliao) (bilateral), BL23 (Shenshu) (bilateral), SP6 (Sanyinjiao) (bilateral), KI3 (Taixi) (bilateral), BL39 (Weiyang) (bilateral), BL28 (Pangguangshu) (bilateral) and CV4 (Guanyuan).

All acupuncture treatment sessions will be performed by two acupuncturists who are registered Chinese Medicine Practitioners in Hong Kong and have at least 3 years clinical experience in acupuncture practice. Interventions will be conducted according to Standards for Reporting Interventions in Controlled Trials of Acupuncture (STRICTA) and ICH-GCP guidelines. To ensure the consistency of skill of various acupuncturists, several training workshops will be provided to acupuncturists who are involved in the study prior to the commencement of the study.

#### Active acupuncture group

Sterile disposable stainless steel needles of various lengths and diameters (Huatuo, Suzhou, China; 0.3 mm × 25 mm/0.3 mm × 40 mm/0.3 mm × 75 mm) will be used in the intervention group. The acupuncture treatment will be administered twice per week, which mimics the clinical practice of using acupuncture treatment for OAB in many Chinese medicine clinics in Hong Kong, and the whole treatment period will last for 8 consecutive weeks. A total of 16 sessions of acupuncture treatment will be administered to each participant.

#### Sham acupuncture group

In this study, participants randomized to the placebo-control arm after baseline assessment will receive sham acupuncture in addition to standard routine care. The sham acupuncture used in this study is a type of acupuncture in which needles are of the same size as those used in the intervention group; however, the needles will not penetrate the skin; instead, the needles are retracted into the needle handle instead of penetrating the skin and are directed at the same points as are used in the active treatment group. As such, subjects will experience a non-penetrating pricking sensation instead of *de-qi* feeling, characterized as soreness, numbness, heaviness and feeling of pressure.

The sham acupuncture device we will use is known as Park Sham Device (Dong Bang Acupuncture Inc., Korea), which consists of a base with a hole in the center and sticky tape on the bottom. The sham acupuncture device is specifically designed for sham-acupuncture-controlled trials, and makes it impossible for the subject to see whether or not the needle has penetrated the skin. Each Park Sham Device is composed of a needle and a series of components, for instance, an adhesive tube, a guide tube, the Park tube and a flange [17]. The structure of the Park Sham Device is shown in Fig. 2.

**Fig. 2 Fig2:**
[figure not shown]
Structure of the Park Sham Device. Park Sham Device with sham needle and real needle. 1. Needle handle, 2. Guide tube, 3. Guide O-Ring, 4. Park tube, 5. Flange, 6. Double sided tape, 7. Skin 8. Dermis, 9. Muscle, 10. Dull tip of sham needle, 11. Sharp tip of real needle

As an incentive measure for patient compliance and for ethical considerations, for patients who are assigned to the sham acupuncture group, we will provide free acupuncture treatment for their OAB after they have completed the entire study including the follow-up period (Table 1).

**Table 1 Tab1:** Locations, therapeutic indications and manipulations of the acupuncture points selected in this study

Points	Location	Indications	Manipulation
BL32 (次髎)	On the sacrum, medial and inferior to the posterosuperior iliac spine, just at the 2nd posterior sacral foramen	Lumbago, hernia, irregular menstruation, abnormal discharge, dysmenorrheal, emission, impotence, enuresis, dysuria, flaccidity of lower extremities	Puncture perpendicularly to a depth of 1.2 cun, then apply reinforcing technique with the lifting and thrusting movement for 30 s
BL23 (腎俞)	On the lower back, below the spinous process of the 2nd lumbar vertebra, 1.5 cun lateral to the posterior midline	Emission, impotence, enuresis, irregular menstruation, leukorrhagia, lumbago, soreness and weakness of the waist and knee, dizziness and vertigo, tinnitus, deafness, edema, dyspnea, diarrhea	Puncture perpendicularly to a depth of 1.2 cun, then apply reinforcing technique with the lifting and thrusting movement for 30 s
SP6 (三陰交)	On the medial side of the leg,3 cun above the tip of the medial malleolus, posterior to the medial border of the tibia	Abdominal pain, borborygmus, distention of the abdomen, diarrhea, dysmenorrhea, irregular menstruation, metrostaxis and metrorrhagia, abnormal vaginal discharge, prolapse of the uterus, infertility, dystocia, emission, impotency, enuresis, dysuria, edema, hernia, pain in the vulva, flaccidity of the lower extremities, headache, dizziness, insomnia	Puncture perpendicularly to a depth of 1.0 cun, then apply reinforcing technique with the lifting and thrusting movement for 30 s
KI3 (太溪)	On the medial border of the foot, posterior to the medial malleolus, in the depression between the tip of the medial malleolus and Achilles tendon	Dry and sore throat, toothache, deafness, tinnitus, dizziness, hemoptysis, dyspnea, diabetes mellitus, irregular menstruation, insomnia, emission, impotence, frequency of micturition, lumbago	Puncture perpendicularly to a depth of 0.8 cun, then apply reinforcing technique with the lifting and thrusting movement for 30 s
BL39 (委陽)	At the lateral end of the popliteal crease, medial to the tendon of the biceps muscle of the thigh	Stiffness of the back and lumbar region, distention of the lower abdomen, edema, dysuria, contraction of the leg and foot.	Puncture perpendicularly to a depth of 1.0 cun, then apply reinforcing technique with the lifting and thrusting movement for 30 s
BL28 (膀胱俞)	On the sacrum and on the level of the 2nd posterior sacral foramen, 1.5 cun lateral to the median sacral crest.	Interrupted urination, enuresis, frequency of micturition, diarrhea, constipation, stiffness and pain in the back and lumbar region	Puncture perpendicularly to a depth of 1.0 cun, then apply reinforcing technique with the lifting and thrusting movement for 30 s
CV4 (關元)	On the lower abdomen and on the anterior midline, 3 cun below the center of the umbilicus	Enuresis, nocturnal emission, frequency of micturition, retention of urination, hernia, irregular menstruation, abnormal vaginal discharge, metrorrhagia and metrostaxis, postpartum hemorrhage. Pain in the lower abdomen, indigestion, diarrhea, rectal prolapse, apoplexy marked by prostration syndrome	Puncture perpendicularly to a depth of 1.0 cun, then apply reinforcing technique with the lifting and thrusting movement for 30 s

### Outcomes

#### Primary outcome

Among these variables, the primary outcome measurement is change in the frequency of incontinence episodes [2]. The 7-day voiding diary, which records daily micturition and symptoms, such as the time of micturition, voided volume per micturition and incontinence episodes in the most recent 7 days. The 7-day voiding diary is chosen based on the following reasons: (a) the validity of the scale has been proven by a previous study, (b) it was found to provide more accurate information than the 3-day voiding diary [18], (c) it is a non-invasive assessment tool, which minimizes the risk and inconvenience to the patient and (d) the Chinese version of the diary has been validated and is readily available for use.

#### Secondary outcomes

##### Urinary NGF

Lack of objective outcome assessment is a major limitation of the previous studies on OAB. Aydogus et al. [19] conducted a pioneer placebo-controlled clinical trial of acupuncture for treating OAB using NGF as a biological marker for treatment outcome. It was reported that the decrease in urinary NGF caused by acupuncture and solifenacin treatment correlated well with the improvement in OAB symptoms. Based on these findings, we propose to use urinary NGF as a secondary outcome in the present study. The urine sample will be collected from each participant at baseline and weeks 8 and 20 (follow up) and the urinary NGF will be measured by ELISA. The laboratories at the School of Chinese Medicine, CUHK have all the necessary facilities to conduct the ELISA [20] (Table 2).

**Table 2 Tab2:** Summary of outcome measurements at different time points

Outcome measurements	Data collection instrument	Baseline	Treatment	Follow up
			Week 8 (end of treatment)	Week 20 (end of follow-up period)
The 7-day voiding diary	Diary	✓	✓	✓
Urinary NGF level	ELISA	✓	✓	✓
IIQ-7	Questionnaire	✓	✓	✓
UDI-6	Questionnaire	✓	✓	✓
Adverse events	Adverse event report form		✓	

*NGF* nerve growth factor, *IIQ-7* Incontinence Impact Questionnaire, *UDI-6* Urogenital Distress Inventory

##### Incontinence Impact Questionnaire (IIQ-7), Overactive Bladder Symptom Score (OABSS) and Urogenital Distress Inventory (UDI-6)

Besides urinary NGF, the outcomes recommended by the ICS, such as IIQ-7 and UDI-6 will also be used as secondary outcome measures [21]. The IIQ-7 and UDI-6 chosen for this study are available in Chinese versions, which are known to be as sensitive, valid and reliable as the original version and other languages [22]. Moreover, a simple self-report questionnaire consisting of four symptoms - daytime frequency, night-time frequency, urgency and urgency incontinence will also be used as a secondary outcome [23].

All of the primary and secondary outcomes will be collected at baseline, the end of treatment (2 months after inclusion) and 3 months after the completion of treatment. The schedule of enrolment, intervention and assessments is shown in Fig. 3.

**Fig. 3 Fig3:**
[figure not shown]
Schedule of enrollment, intervention and assessments of this study protocol

### Adverse events

All adverse events as defined by ICH-GCP guidelines will be fully recorded on the adverse event pages of the case report forms (CRFs). Signs and symptoms of each adverse event will be described in detail such as date of onset, intensity, outcome, date of resolution and any action taken. The adverse events will be tabulated in each group and the incidences calculated. Serious adverse events will be reported to the Research Ethics Committee concerned within 24 h. If any serious adverse effect occurs, emergency medical assistance will be sought and all details noted. The adverse events are recorded for the purpose of evaluating the safety of acupuncture treatment.

### Sample size estimation

The primary outcome measure is post-treatment incontinence episodes as derived from the 7-day bladder diary. Based on a previous study of Emmons and Otto [2], the placebo effect was 40% reduction in incontinence episodes among patients treated with placebo acupuncture. To detect a clinically meaningful effect of 30% difference in the change of frequency of incontinence episodes between the treatment and placebo control group, 41 cases will be needed in each group to have 80% power to detect difference between the two groups at the significance level of 0.05. To allow for a predicted dropout rate of 20%, a total of 100 patients will be required for this study, with 50 patients in each arm.

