### Statistical analysis

All analyses will be conducted according to the intention-to-treat principle. Descriptive statistics will be computed for each of the analyzed variables. The baseline characteristics will be tabulated and some of large differences between the two groups will be noted and examined in the general mixed model. The generalized linear mixed model will be used to compare primary and secondary outcomes between groups and test correlation between baseline factors, including NGF level, and the primary and secondary outcomes. Per-protocol analysis will be also performed. All statistical tests will be two-sided, and *p* < 0.05 is considered statistically significant. The statistical software of SPSS (SPSS, SPSS Inc., Chicago, USA) version 23.0 will be used for the analysis.

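### The 80% power stated for 41 per arm is not shown to hold for the primary outcome: no SD is printed, and the inputs fit a comparison of two proportions

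*Protocol article*

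**What the plan says.** All of this is in the protocol article.

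- **Outcome.** The Primary outcome section says "the primary outcome measurement is change in the frequency of incontinence episodes". The Sample size estimation section words it as "The primary outcome measure is post-treatment incontinence episodes as derived from the 7-day bladder diary". Either way it is a number recorded for each patient. Neither section defines a responder.
- **Inputs.** The sample size section takes from an earlier study that "the placebo effect was 40% reduction in incontinence episodes among patients treated with placebo acupuncture" and sets the target as "To detect a clinically meaningful effect of 30% difference in the change of frequency of incontinence episodes between the treatment and placebo control group".
- **Result.** "41 cases will be needed in each group to have 80% power to detect difference between the two groups", "at the significance level of 0.05". Allowing for 20% dropout, the trial enrols 50 per arm, 100 in total.
- **Analysis.** The Statistical analysis section says "The generalized linear mixed model will be used to compare primary and secondary outcomes between groups", and "All statistical tests will be two-sided".

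The sample size paragraph prints no SD, baseline episode rate, dispersion parameter, test or formula.

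**The concern.** For a quantity measured on each patient, power depends on the difference and on the between-patient spread. The paragraph gives the difference but no spread. It does give the sham level of 40%. A comparison of means with a given SD does not need that level, whereas a comparison of two proportions does, because there the level fixes the variance through p(1−p). That, with the numerical match below, suggests that a percentage reduction in episodes was entered as if it were a percentage of patients.

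If so, the 80% belongs to a different endpoint from the one that will be analysed. The article presents the trial as full-scale, in contrast to earlier studies with small samples, and that description leans on this calculation. Readers of a non-significant result would take the 80% as a measure of how well a 30-point difference had been ruled out, and the document does not support that use.

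**Working it through.** **Inputs from the protocol article.** Sham reduction 40%; difference 30%, read as percentage points, so 40% vs 70%; two-sided α = 0.05 (z = 1.960); power 80% (z = 0.842); 41 per arm needed, 50 enrolled, 20% dropout, so 50 × 0.80 = 40 completers per arm.

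**Step 1. Reproduce the stated 41 as two proportions.** With p₁ = 0.40, p₂ = 0.70 and mean 0.55:

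- Pooled: n = [1.960·√(2·0.55·0.45) + 0.842·√(0.40·0.60 + 0.70·0.30)]² / 0.30² = (1.379 + 0.565)² / 0.09 = 41.97.
- Arcsine: h = 2·asin√0.70 − 2·asin√0.40 = 0.613; n = 2·(1.960 + 0.842)² / h² = 41.79.
- Unpooled: n = (1.960 + 0.842)²·0.45 / 0.09 = 39.24.
- Pooled with continuity correction: 49 after rounding up.

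The pooled and arcsine results are within one patient of 41, and pooled power at 41 per arm is 79.0%. Other readings are far off: 40% vs 52% (30% taken as relative) needs 270 per arm, and 40% vs 10% needs 32. No variant rounds up to exactly 41.

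**Step 2. Reproduce 41 as two means.** The printed inputs do not allow this, because there is no SD. Solving backwards, a two-sample t-test with 41 per arm has 80% power at a standardized difference of 0.626, so SD = 30 / 0.626 = 47.9 points. The normal approximation gives 30 / [√(2/41)·(1.960 + 0.842)] = 48.5 points. An unprinted SD of about 48 points would therefore also produce 41. With 40 per arm, the t-test SD that gives 80% is 30 / 0.634 = 47.3 points.

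**Step 3. Power on the scale of the outcome.** This uses a 30-point difference in mean percentage change, an unadjusted two-sided t-test and 40 completers per arm. The SDs are assumptions, since the document gives none.

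| Assumed SD (points) | Power |
|---|---|
| 40 | 91% |
| 45 | 84% |
| 50 | 76% |
| 60 | 60% |
| 70 | 47% |
| 80 | 38% |

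**Step 4. Effect of baseline adjustment.** If baseline correlates with the outcome at an assumed 0.5, the residual SD for an SD of 50 is 50·√(1 − 0.25) = 43.3 points, and power at 40 per arm rises from 76% to 86%. The table is thus a guide to how strongly power depends on the SD, and does not give the power of the planned mixed model.

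**The case against.** The strongest reply is that the formula is not named, so its origin can only be inferred. The numerical match is close but not exact, a comparison of means with an SD near 48 points gives 41 as well, and the 40% sham figure could have been printed as background. This stands: the two-proportion origin is a strong inference and not a fact, and one cannot say that no SD was used, only that none is printed.

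A second reply is that a journal article condenses the full protocol, where the SD and formula may be given. That is fair for the omission taken alone. What remains is that the figures the article does print lead to about 41 through a method that does not fit the outcome and model it states.

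A reader might go further and infer that the trial is underpowered. The documents do not support that. The spread of the outcome is unknown, an SD of 40 or 45 points gives more than 80% power, and the planned model may gain from baseline adjustment and from partially observed patients under intention-to-treat.

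Finally, type I error, the treatment estimate and its confidence interval do not depend on the planning calculation, and the interval offers some protection against misreading a null result. That is right, and it limits the seriousness of the point.

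**Conclusion.** The point holds in a limited form: the 80% power is not shown for the primary outcome. The printed inputs reproduce about 41 to 42 per arm as a comparison of 40% with 70% of patients, whereas the outcome is a per-patient change in episodes to be analysed in a generalized linear mixed model. For a 30-point difference in mean percentage change, the claim needs an SD of about 48 points or less at 41 per arm (about 47 at 40 per arm) without baseline adjustment. Over assumed SDs of 40 to 80 points, power at 40 per arm runs from 91% to 38%, on both sides of the stated figure. These results rest on reading the 30% as percentage points and on SDs that the document does not supply. The plan should be corrected, but the point does not threaten the validity of the comparison.

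**What to change.** Keep 100 patients. Replace the sample size paragraph with a calculation for the outcome and model that will be analysed. It should state:

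- the planned contrast, for example mean reductions of 40% and 70%, which leave 60% and 30% of baseline episodes, a ratio of 0.5;
- the assumed SD or dispersion and its source, or the blinded pooled SD from this trial;
- the baseline adjustment assumed.

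Then restate the power, or the detectable difference, for 40 to 41 completers per arm, and keep the 80% claim only if it holds on that scale. If an SD near 48 points was in fact used, printing it with its source and the formula would settle the matter.

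The cost is one rewritten paragraph and a short calculation, with no extra patients and no change to procedures. The downside is that the stated power may become less favourable.

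### Fifty patients per arm less the predicted 20% dropout leaves 40, one short of the 41 per arm that the protocol says it needs

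*Protocol article*

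**What the plan says.** All the figures stand in one paragraph of the protocol article, under Sample size estimation. The requirement is that "41 cases will be needed in each group to have 80% power", at a significance level of 0.05. The allowance for losses follows: "To allow for a predicted dropout rate of 20%, a total of 100 patients will be required for this study". The paragraph divides this total equally, 50 to an arm. The Abstract repeats the total of 100, and Study design repeats 100 with 50 per group at 1:1.

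The paragraph does not say how the dropout allowance was calculated. It also names no test and gives no standard deviation for the 41. The Statistical analysis section adds that "All statistical tests will be two-sided", and plans an intention-to-treat analysis with a generalized linear mixed model, plus a per-protocol analysis.

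**The concern.** A dropout allowance exists so that the required number is still available after the predicted losses. Here the required number, the predicted rate and the enrolment figure are all printed, and the third does not follow from the first two. The check needs no outside source and no assumption about the test.

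What is at stake is the accuracy of a statement that is normally carried into the results report. Left as it is, that report would say that 100 patients protect 80% power against 20% dropout, which the protocol's own numbers contradict. Conduct of the trial is not affected.

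**Working it through.** **Inputs**, all from Sample size estimation unless noted:

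- required per arm: 41
- predicted dropout: 20%
- planned enrolment: 50 per arm, 100 in total
- power 80%, significance level 0.05; two-sided, from Statistical analysis

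**1. Where the 50 may come from.** Adding 20% to the required number gives 41 × 1.20 = 49.2, which rounds up to 50. This matches the stated figure exactly. It applies the dropout rate to the completers instead of to those enrolled. Since the protocol does not state its formula, this route is an inference. The inconsistency below does not depend on it.

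**2. What 50 per arm leaves.** 50 × (1 − 0.20) = 40 per arm, against the 41 required: a shortfall of 1.

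**3. What 41 would need at 20% dropout.** 41 / (1 − 0.20) = 51.25, so 52 per arm and 104 in total. Rounding only the total gives 82 / 0.80 = 102.5, so 103, but equal arms need 104.

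**4. What dropout 50 per arm can absorb.** (50 − 41) / 50 = 9/50 = 18%.

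**5. What the shortfall costs in power.** The protocol does not give enough to compute power directly. The loss can be scaled by taking 41 per arm to give exactly 80% and letting precision grow with the square root of n (normal approximation, two-sided 0.05):

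power(n) = Φ[(1.960 + 0.842) × √(n/41) − 1.960]

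- n = 41: Φ(0.842) = 80.0%
- n = 40: 2.802 × √(40/41) = 2.767; 2.767 − 1.960 = 0.807; Φ(0.807) = 79.0%

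The cost is about one percentage point.

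| Quantity | Stated | Recalculated |
|---|---|---|
| Enrolled per arm to keep 41 at 20% dropout | 50 | 52 |
| Total enrolled | 100 | 104 |
| Remaining per arm from 50 at 20% dropout | 41 (implied) | 40 |
| Dropout at which 50 per arm keeps 41 | 20% | 18% |
| Power at 20% dropout | 80% | about 79% |

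**The case against.** The strongest objection is size. One patient per arm is a small gap, 20% is only a prediction, and 18% against 20% is well within the uncertainty of any such forecast. A one-point change in power would not alter how a non-significant result is read. All of this stands, and it limits the point to a minor one. It does not make the three printed figures agree.

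A second objection is that dropouts are not wholly lost. Under intention-to-treat with a mixed model, a patient who leaves after the week 8 assessment still contributes end-of-treatment data, so 40 is a cautious count. That is fair in part. But the paragraph itself enlarges the sample for dropout, so by its own logic dropouts do not count towards the 41. Outcomes are collected only at baseline, week 8 and week 20, so a patient lost before week 8 has no post-treatment diary.

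Two stronger readings are tempting, and the document supports neither.

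- *That the 41 is itself wrong.* A reader might treat the 40% placebo reduction and the 30% difference as responder proportions of 40% and 70%, recalculate the 41, and build a larger total on the result. The protocol describes these figures as a reduction, and a difference in the change, in episode frequency. It does not call them proportions of patients. Even on the two-proportion reading, the common formulas fall on both sides of 41: 39.24 with unpooled variance (40 after rounding up), 41.79 with the arcsine method and 41.97 with pooled variance (both 42). With unpooled variance, 40 per arm would still give 80.7% power. No corrected base number, and no power figure specific to one of these formulas, can be attributed to the protocol.
- *That the trial is materially underpowered, or should enrol more.* A gap of one evaluable patient per arm does not show that.

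**Conclusion.** The point holds as a minor arithmetic inconsistency. That 50 less 20% is 40, below the stated 41, is certain and rests only on the printed figures. The 79% is conditional: it takes 41 per arm as giving exactly 80% power, uses a normal approximation, and counts every dropout as lost to the analysis. If some dropouts contribute week 8 data, the loss is smaller. Whether 41 is the right starting number cannot be judged from this article, and that question is no part of the conclusion.

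**What to change.** Reword the last sentence of Sample size estimation and leave enrolment at 100. Suggested text: *One hundred randomised patients (50 per arm) retain 41 per arm with up to 18% dropout. With 20% dropout, 40 per arm remain, and power is about one percentage point below the stated 80% (about 79% if 41 per arm gives exactly 80%).* Use the same wording in the results report.

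The cost is a change of wording in one paragraph and a slightly less favourable statement. The total of 100 in the Abstract and in Study design can stay, and no change to conduct or analysis follows.
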